### Withdrawals, discontinuation and post-trial care

Acupuncture is a low-risk intervention and any adverse effects are usually minimal and temporary. In the event of mild adverse effects (drowsiness, haematoma, bleeding from a point, stuck needle, pain after needling a point) participants will not be withdrawn but will be able to drop out if they so wish. In the event of the occurrence of more serious adverse events, participants will be withdrawn. As evidence suggests that acupuncture is a safe treatment [27,28] and as this study is not assessing effectiveness, no specific arrangements have been made to review interim safety and effectiveness. However, in the event of three participants reporting prolonged aggravation of pain or other potential serious adverse events, the trial will be stopped prematurely. After completion of the study, participants will be offered access to acupuncture through their general practitioner or physiotherapist.

### Concomitant care

Participants will be asked to refrain from using other forms of complementary therapy for the duration of the trial but may receive any intervention as routinely prescribed by clinical staff at the Amputee Rehabilitation Unit.

### Study restrictions

Participants and practitioners will be asked not to disclose participant allocation to the researcher ([name]).

### Intervention (interviews)

Consecutive sampling will be used to recruit (*n* = 5) participants from group A to explore their experience of being in the trial, having acupuncture and completing outcome measures. Participants will be interviewed once after completion of the study. Semi-structured interviews will be facilitated by [name], will follow a topic guide (Additional file 1) and will be recorded and transcribed verbatim.

### Randomization, allocation concealment and blinding

Randomization and allocation concealment will be used to ensure against selection bias [29]. Prior to commencement of the study, a researcher (NR) not involved in the day-to-day execution of the study will randomly allocate and conceal allocation. A copy of the randomized sequence will be kept in a locked cabinet and not shared with study personnel. The researcher ([name]) who will enrol participants and assign them to either acupuncture intervention or control will not know the random sequence or treatment allocation.

Randomization will be achieved using a computer-generated random numbers table and will be unstratified and balanced (1:1). Permuted blocking will be used to achieve balance between study arms. A block size of four will be used in this study. Allocation concealment will be implemented using sequentially numbered, opaque sealed envelopes. The envelopes will be opened sequentially only after participant’s details are written on each envelope.

Participants and practitioners involved in the study will not be blinded. However, the researcher collecting outcome measures ([name]) will be blind to the participant’s allocation.

### Outcome measures

Recommendations from the Assessment Committee of the Neuropathic Pain Special Interest Group [30] and the Initiative on Methods, Measurements, and Pain Assessment in Clinical Trials [31] were taken into consideration when developing outcome measures for use in this trial.

The primary outcome measure will be an 11-point numerical rating scale to record pain intensity. Pain will be rated by a number describing average pain over the previous week, using the anchors 0, meaning ‘no pain’, and 10, meaning ‘pain as bad as you can imagine’ [31]. The numerical rating scale is an appropriate measure of pain intensity [32] and is a recommended outcome measure for clinical trials of chronic pain treatment effectiveness [31].

Secondary outcome measures will include a numerical rating scale measuring ‘worst’ pain, the short-form McGill Pain Questionnaire 2 (SF-MPQ-2), EQ-5D-5 L, Hospital Anxiety and Depression Scale, 10-Item Perceived Stress Scale, Insomnia Severity Index, and Patient Global Impression of Change.

The McGill Pain Questionnaire and its short form (SF-MPQ) are generic questionnaires (applicable to any pain), whose reliability and validity have been extensively documented [33]. The SF-MPQ-2 is a 22-item questionnaire that uses a 10 point rating scale and records the major symptoms of both neuropathic and non-neuropathic pain [34]. It is reliable and valid for measuring diverse chronic pain [35].

The EQ-5D measures health-related quality of life and although not validated for use in neuropathic trials, results appear robust in neuropathic trials with a large sample size or when recording a large-pain relief response in the active group [30]. The EQ-5D-5 L has the same core dimensions as the EQ-5D but instead of a three-point rating scale it uses five levels.

The Hospital Anxiety and Depression Scale measures emotional function and is responsive to change in neuropathic pain clinical trials [30]. It includes seven depression and seven anxiety items to cover cognitive and emotional aspects of depression and anxiety and is reliable and valid for assessing emotional distress in a medical population [36].

The Perceived Stress Scale is a 4-, 10- or 14-item questionnaire that was designed to measure psychological stress [37]. It is reliable and valid and was found to have acceptable psychometric properties across 19 studies [38]. The 10-item version has no loss of psychometric quality, compared with the 14-item version [39] and has, in fact, been shown to be superior [38].

The Insomnia Severity Index measures perception of insomnia and the degree of concerns or distress caused by insomnia; it consists of seven items [40]. It has the advantage of measuring symptoms over a 2-week period and is recommended when insomnia is a secondary endpoint. It has been validated against both polysomnographic and prospective sleep diary measures [40,41].

The Patient Global Impression of Change scale is advised for use in clinical trials [30,31] and provides a readily interpretable assessment of participants evaluation of the importance of their improvement [42]. The scale used in this study will be a seven-point scale that ranges from ‘no change or worse’ to ‘a great deal better’ [43].

### Assessment

Participants will complete the questionnaires and rating scales six times in total. Data for all items (except the Patient Global Impression of Change, data for which will only be collected from the end of week one) will be collected at the time of enrolment and at the end of each week for the duration of the study. The primary endpoint will be at the end of the intervention (end of week 4). Data for the outcome measures will also be determined one month after completion of the study. Questionnaires and rating scales will be completed under the supervision of the researcher ([name]) at baseline and during weeks 1 to 4 (whilst participants are inpatients at the Amputee Rehabilitation Unit), and will be posted to participants one month after completion of the study.

### Analysis

As this is a feasibility study, emphasis will be on feasibility and not on statistical significance of results [21]. Compliance with the protocol will be examined through number counts on drop outs or numbers of missed treatments, completion rates of outcome measures, and their perceived appropriateness and deviation from the protocol. Data will be collected on the use of rescue medication and adverse events (captured through open-ended prompts by practitioners at each intervention time point). Details of any participants who are excluded from the study will be reported and exclusion will be distinguished from attrition.

All statistical analysis will be undertaken using SPSS Version 21 software. The analysis will test for within-patient and between-group differences in measurements taken at the beginning of the study, during the study, at the end of the study and one month after completion of the study. An intention-to-treat approach will be taken [44]. To include missing data, any missing data will be imputed using the last observation carried forward [45].

The null hypothesis is that there is no difference in change in the primary outcome measure between group A and C at the end of intervention (end of week 4). Statistical analysis will be performed to verify rejection of the null hypothesis with a *P* = 0.05 taken as indicative of statistical significance. Nonparametric tests will be used in inferential analysis. The nonparametric Mann–Whitney *U* test will be used for analysis between groups. The difference between baseline and last observation scores will be analyzed using Wilcoxon signed-rank test. The effect size (Cohen’s *d*) will be calculated to provide information on the relative magnitude of difference [46]. All secondary outcome measures will be treated in the same way as the primary outcome. Categorical and continuous baseline characteristics will also be analyzed to test for between-group differences.

A framework analysis procedure [47] will be used to analyze qualitative data. NVivo 10 software will be used to develop the analytic framework and index transcripts. Microsoft Excel will be used during charting. Interviews will be transcribed verbatim. Specific steps will be followed during data analysis, including; familiarization, coding, identifying an analytic framework, indexing, charting and mapping or interpretation. To ensure credibility, peer debriefing will take place throughout the research process. To ensure dependability, two researchers will separately code a selection of transcripts.

The trial will be considered successful if:Recruitment rate is ≥2 participants per month fitting the eligibility criteria.The study recruits ≥70% of all eligible potential participants.Of the participants recruited to group A, ≥90% receive their first acupuncture treatment within one week of recruitment.After randomization and allocation, ≥90% of participants receive treatment as initially intended.Of the participants recruited to group A, ≥80% receive all eight acupuncture treatments.Of the participants recruited to group C, ≤10% drop out of the study.At the primary endpoint of the study, questionnaires and rating scales for outcome measures are completed by ≥90% of participants.At one month after completion of the study, questionnaires and rating scales for outcome measures are completed by ≥60% of participants.Qualitative data identifies that outcome measures are acceptable and appropriate, that questionnaires and rating scales are easy to complete and that outcome measures can be identified for used in a definitive trial.Qualitative data implies that acupuncture is an acceptable and effective intervention for treating phantom limb pain with or without other secondary symptoms.Qualitative and quantitative data implies that the acupuncture protocol used in the feasibility study is appropriate for use in a definitive multicentre randomized controlled trial.

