**Methods/design:**

An unstratified, pragmatic, randomized, two-armed, controlled trial of parallel design comparing acupuncture and usual care control will be conducted. A total of 20 participants will be randomly assigned to receive either usual care or usual care plus acupuncture. Acupuncture will include eight 1 hour treatments delivered pragmatically over 4 weeks by practitioners trained in traditional Chinese medicine. As outcome measures, the Numerical Pain Rating Scale, short-form McGill Pain Questionnaire 2, EQ-5D-5 L, Hospital Anxiety and Depression Scale, 10-Item Perceived Stress Scale, Insomnia Severity Index, and Patient Global Impression of Change will be completed at baseline, weekly for the duration of the study and at 1 month after completion of the study. After completion of the trial, participants will provide feedback though semi-structured interviews.

Feasibility will be determined through the ability to recruit to the study, success of the randomization process, completion of acupuncture intervention, acceptability of random allocation and completion of outcome measures. Acceptability of the acupuncture intervention will be determined through semi-structured interviews with participants. The appropriateness of outcome measures for a future trial will be addressed through completion rates of questionnaires and participant feedback.

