### Recruitment

Participants will be approached and recruited whilst they are inpatients at the Amputee Rehabilitation Unit. Newly admitted potential participants will be identified by clinical staff (JG, CC), approached by the researcher ([name]), initially screened, and provided with oral and written information. Participants who pass initial screening tests and are willing to participate will have a final eligibility check by [name] before enrolment in the study (Figure 1). Signed, informed consent will be obtained from all participants before enrolling them in the study. Those declining to participate will be asked briefly for their reasons. As the study is a feasibility study, no sample size calculation has been performed [21]. An arbitrary number of 20 participants was deemed adequate to provide information on recruitment, randomization and acceptability of acupuncture and answer the objectives of this trial [23].

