### Intervention (RCT)

The acupuncture group (group A) will receive usual inpatient care and a course of acupuncture. The control group (group C) will receive usual inpatient care only. Usual care will include both medical intervention and daily physiotherapy and rehabilitation, as routinely provided at the Amputee Rehabilitation Unit.

All acupuncture practitioners involved in the study will be trained in the practice of traditional Chinese medicine. All practitioners will be members of the British Acupuncture Council, will have at least 15 years clinical experience and will follow the safety guidelines of the British Acupuncture Guide to Safe Practice [25]. Acupuncture needles will be single-use, presterilized, disposable, solid, stainless steel needles (with prepacked single-use guide tubes if guide tubes are used). The acupuncture intervention will be pragmatic but will be guided by a protocol previously developed though a Delphi practitioner consensus study [26]. This protocol advises:Using a combination of body and auricular acupuncture;Treating the contralateral limb and possibly the ipsilateral limb;Including auricular acupuncture points such as shen men, sympathetic and points corresponding to the lower limb;Depending on the health of the tissue and the individual participant, needling around the stump;Mirroring local and distal points by needling the opposite limb;Including points on the lower back (taking a segmental approach to dermatomal pain);Including points such as LI4 + LR3, LR3, GV20, SP10 and also specified points according to participants’ specific symptoms;Retaining needles for 20 to 30 minutes.

No set criteria will be followed when needling, other than to follow the guidelines of the protocol. Practitioners will assess and treat participants under the paradigm of traditional Chinese medicine. Treatment may (depending on the practitioner’s diagnosis and treatment plan) include electro-acupuncture or other adjunctive interventions, such as cupping. All participants in group A will receive eight one-hour acupuncture sessions (twice weekly for 4 weeks) delivered during their inpatient stay.

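### The only adverse-event prompt the article states exists in the acupuncture arm alone, so general adverse-event counts reported by arm would be inflated in group A through ascertainment

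*Protocol article*

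**What the plan says.** The Analysis section says that data on rescue medication and adverse events will be collected, and adds in parentheses "captured through open-ended prompts by practitioners at each intervention time point". The article gives no other route for recording adverse events.

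Under Intervention (RCT), the practitioners are the people who deliver acupuncture: "All acupuncture practitioners involved in the study will be trained in the practice of traditional Chinese medicine". The sections on study restrictions and on blinding use the word in the same sense, while ward personnel are called clinical or medical staff. The sessions belong to one arm: "All participants in group A will receive eight one-hour acupuncture sessions (twice weekly for 4 weeks". For the other arm, "The control group (group C) will receive usual inpatient care only".

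The Assessment section describes contact that both arms share: questionnaires at enrolment and at the end of each of weeks 1 to 4, supervised by the researcher, and a posted set one month after completion. It attaches no adverse-event question to any of these.

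The section on withdrawals and discontinuation gives a trial-level stop: "in the event of three participants reporting prolonged aggravation of pain or other potential serious adverse events, the trial will be stopped prematurely". It names no arm, and it says that no specific arrangements exist for interim safety review.

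**The concern.** The capture method depends on a contact that only group A has. A general event, such as a fall, an infection or a flare of pain, would be asked about in one arm and recorded in the other only if it happened to come to notice. If the two arms had the same true event risk, a table of adverse events by arm would still tend to show more in the acupuncture arm.

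Three further matters follow.

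- **Follow-up.** No adverse-event prompt is stated after the eighth session in either arm, although outcome follow-up runs for another month.
- **Rescue medication.** The parenthesis directly follows the words on adverse events, but it can also be read as covering rescue medication. If so, those data have the same asymmetry, and they bear on how pain scores are read.
- **Stopping count.** The count of three participants is not limited to an arm, while the stated prompt is.

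The trial is meant to inform the protocol of a definitive study. A recording procedure that runs in one arm leaves the two-arm procedure untested.

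**Working it through.** The article states no figure for event risk or safety precision, and it says that "no sample size calculation has been performed", so there is no figure of the plan's own to reproduce. The check counts prompts and then shows what unequal capture does over a range of assumed risks.

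**Inputs from the article**

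- Sample size: "A total of 20 participants will be randomly assigned to receive either usual care or usual care plus acupuncture" (Abstract, Methods/design).
- Allocation: "will be unstratified and balanced (1:1"), in blocks of four (Randomization section). 20 / 4 = 5 complete blocks, so 10 per arm if 20 are recruited.
- Sessions: 8 per participant in group A, none in group C (Intervention section).
- Shared assessments after baseline: 4 weekly and 1 postal (Assessment section).

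**Scheduled adverse-event prompts as written**

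- Group A: 10 × 8 = 80 at most, fewer if sessions are missed.
- Group C: 10 × 0 = 0.

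**Expected number of participants with an event on record**

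Let p be the true risk per participant, equal in both arms, and s the share of affected control participants whose events surface without a prompt. Both are assumptions, since the article gives neither. Capture in group A is taken as complete. Then:

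- expected on record in A = 10 × p
- expected on record in C = 10 × p × s
- apparent risk difference = p × (1 − s)

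| p | A | C, s = 0 | C, s = 0.25 | C, s = 0.5 | Apparent difference, s = 0 to s = 0.5 |
|---|---|---|---|---|---|
| 0.10 | 1.0 | 0 | 0.25 | 0.5 | 10 to 5 points |
| 0.20 | 2.0 | 0 | 0.5 | 1.0 | 20 to 10 points |
| 0.30 | 3.0 | 0 | 0.75 | 1.5 | 30 to 15 points |

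The true difference is zero in every row.

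**Stopping count**

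The probability that at least three participants report a qualifying event is P(X ≥ 3), with X binomial (n, p). Use n = 10 if only group A reports count and n = 20 if both arms are asked alike. Here p is the assumed risk of an event that counts toward the stop.

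| p | n = 10 | n = 20 |
|---|---|---|
| 0.05 | 0.012 | 0.076 |
| 0.10 | 0.070 | 0.323 |
| 0.20 | 0.322 | 0.794 |
| 0.30 | 0.617 | 0.965 |

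These are the two extremes. They show that the rule behaves differently according to whose reports count, which the article leaves open. They do not predict how often the trial would stop.

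**Prompts if the shared forms carried the item**

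Weekly: 10 × 4 = 40 per arm. With the postal form: 40 + 10 = 50 per arm, equal in A and C.

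**The case against.** The strongest reply is that the article plans no safety comparison. Adverse events appear in a paragraph on protocol compliance. They are not among the eight objectives, the listed outcomes or the success criteria, and the Discussion says that hypothesis tests serve only to pilot procedure. This stands. A reader might infer that a planned between-arm safety analysis is biased by construction, but the article contains no such analysis. The bias concerns counts that may be reported by arm.

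A reader might also infer that control participants have no ascertainment at all. The documents do not support that. Group C are inpatients with medical care and daily physiotherapy, the article does not say the practitioner prompt is the sole route, and average and worst pain are rated in both arms weekly and at one month. Worsening pain, the first trigger named in the stopping rule, could therefore be seen in either arm. What is missing is a stated route by which such events become adverse-event records.

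The stopping paragraph can be read as being about harm from acupuncture, for which prompts at sessions are a natural choice. That reading is possible, but the wording names no arm, so the two sections still need to be reconciled. Needling effects such as a stuck needle can occur only in group A, and there the practitioner prompt is the right tool.

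The rescue-medication reading is only possible, so it cannot be said that rescue use will be uninterpretable. A striking contrast such as 3/10 against 0/10 needs both a 30% risk and no control event surfacing. It is the top of the range shown, not an expected result.

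It could also be said that a journal article condenses a fuller protocol. That would excuse silence, but here the article states a method, and the method as stated applies to one arm.

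**Conclusion.** The point holds in a limited form. The one adverse-event capture route that the article states operates in group A only, with up to 8 prompts per participant against 0, and no adverse-event prompt is stated for either arm after the last session. If general adverse events are reported by arm, group A will tend to look worse through ascertainment. With an equal true risk of 10 to 30%, about 1 to 3 affected participants would be expected on record in A, against 0 in C if none surface or 0.5 to 1.5 if half do. This rests on 10 participants per arm, complete capture in A, and assumed values for the risk and for spontaneous surfacing in C. The rescue-medication data share the problem only if the parenthesis covers them.

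No listed analysis or success criterion depends on these counts, and the direction of the bias is against acupuncture. The change is therefore a cheap improvement to make, not a defect that undermines the trial.

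**What to change.** 1. Put one identical open-ended item on adverse events and rescue-analgesic use on the existing weekly forms and on the one-month postal form, for both arms.
2. Have that item returned sealed or through ward staff. The researcher who supervises the questionnaires is to stay blind, and free text could reveal allocation.
3. Keep the practitioner prompts for needling-related events, and report these separately for group A only.
4. State in the Analysis section whether rescue-medication data come from the practitioner prompts or from a source common to both arms.
5. Reconcile the section on withdrawals and discontinuation with the Analysis section on which participants and which reports count toward the trial-level stop. Which rule applies is for the trial team to decide.

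The cost is one extra item on forms already in use for 20 participants, a slight added burden for them, and a small remaining risk of unblinding. No extra visits or participants are needed.

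### Last observation carried forward as the only missing-data rule can bias the effect size meant for future planning, most at one month (40% missing tolerated; 10% at week 4)

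*Protocol article*

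**What the plan says.** The Analysis section of the protocol article takes an intention-to-treat approach in which "any missing data will be imputed using the last observation carried forward". The rule is not confined to one outcome: "All secondary outcome measures will be treated in the same way as the primary outcome". Nor is it confined to one visit, because the planned tests cover measurements at the start, "during the study, at the end of the study and one month after completion of the study". The article gives no alternative and no sensitivity analysis.

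Under Assessment, forms are completed under supervision at baseline and in weeks 1 to 4 while participants are inpatients, and the primary endpoint is the end of week 4. The last set "will be posted to participants one month after completion of the study".

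The success criteria in the Analysis section say how much non-completion is acceptable:

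- Week 4: "At the primary endpoint of the study, questionnaires and rating scales for outcome measures are completed by ≥90% of participants".
- One month: "At one month after completion of the study, questionnaires and rating scales for outcome measures are completed by ≥60% of participants".

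On early exits, the section on withdrawals says: "In the event of the occurrence of more serious adverse events, participants will be withdrawn". It does not say whether this means leaving treatment or leaving outcome collection as well.

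The Analysis section plans Cohen's d. The Background (objective 7) and the Discussion part of the Abstract assign the effect size to future sample size calculations.

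**The concern.** Carrying a score forward assumes that nothing changed after the last completed form. That assumption is weakest where it would be used most. By one month the acupuncture course is over. The unit's stay is about 7 weeks (Study settings), so many participants will probably have gone home. For an acupuncture participant who does not return the postal form, the rule assumes that any benefit at week 4 lasted in full, which is the very thing a follow-up visit is meant to find out.

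The article gives no figures for the course of phantom limb pain. Movement in the scores is a reasonable inference: participants are newly admitted, in active rehabilitation, and enter only with pain of at least 5, so regression to the mean is possible.

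At stake is the planning value. If the rule shifts Cohen's d, the definitive trial may be made too small or too large. The tests are run only to pilot the procedure, but that caution does not protect the separate use of d for planning.

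**Working it through.** **Inputs from the article.** Total 20, allocated 1:1, so about 10 per arm. Completion thresholds are 90% at week 4 and 60% at one month. The sample size is declared arbitrary, so there is no calculation of the plan's own to reproduce.

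**Tolerated missing data.**
- Week 4: 20 − 0.90 × 20 = 2 participants (10%).
- One month: 20 − 0.60 × 20 = 8 participants (40%).

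These are thresholds for success, not caps. More could be missing if a criterion fails.

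**Bias formula.** Let m be the missing share in an arm and t the true change after the carried score. If missingness is unrelated to the scores, the bias in the difference (acupuncture minus control) is −mA × tA + mC × tC. A negative difference favours acupuncture.

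**Week 4 (assumed slopes).** Both arms fall 0.5 points per week, and the 2 tolerated losses are both in the acupuncture arm after week 1. Then mA = 2/10 = 0.20, mC = 0 and tA = −0.5 × 3 = −1.5.
- Bias = 0.20 × 1.5 = +0.30 points, against acupuncture.
- At 0.25 points per week: 0.20 × 0.75 = +0.15 points.
- With both losses in the control arm, the signs reverse.
- With one loss per arm and equal slopes: 0.

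**One month (assumed changes after week 4).**

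| Missing, acupuncture / control | Change, acupuncture / control | Bias |
|---|---|---|
| 40% / 40% | 0 / 0 | 0 |
| 40% / 40% | −1 / −1 | 0 |
| 40% / 40% | +1 / 0 | −0.40 |
| 50% / 30% | −1 / −1 | +0.20 |
| 30% / 50% | −1 / −1 | −0.20 |
| 80% / 0% | −1 / −1 | +0.80 |

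The last row puts all 8 missing forms in one arm and is an extreme.

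**Simulation of the relapse case.** Assumed: 10 per arm, SD 2, within-patient correlation 0.6, baseline mean 7, 8 of 20 missing at random at one month, 5,000 runs. Control stays at 7; acupuncture falls to 5 by week 4 and returns to 6.

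| Data used | Mean difference | Median d | SD of the estimated difference |
|---|---|---|---|
| Complete data | −1.00 | −0.57 | 0.79 |
| Carried forward | −1.40 | −0.79 | 0.79 |
| Observed only | −1.00 | −0.58 | 1.04 |

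**Effect on a future trial** (two-sided 0.05, 80% power): n per arm = 2 × (1.960 + 0.842)² / d² = 15.70 / d².
- d = 0.79: 15.70 / 0.624 = 25.2, so 26 per arm.
- d = 0.57: 15.70 / 0.325 = 48.3, so 49 per arm.

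**Missingness related to pain.** If those with more week-4 pain are likelier not to reply and both arms fall by 1 point, a true difference of −2.0 becomes −2.27 with carrying forward and −2.01 with observed cases. If scores are stable after week 4, carrying forward gives −2.05.

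**The case against.** The strongest reply is that this is a feasibility study. Effect size is objective 7 of 8, the Analysis section puts feasibility ahead of significance, and the Discussion says the tests only pilot the procedure. That stands: a reader might infer that the trial exists to produce effect estimates, and the article does not support this. The completion rates, dropout counts and other feasibility criteria are counted separately and are not altered by imputation. Nor is attrition hidden, because dropouts and completion rates are to be reported and CONSORT is to be followed.

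The 40% belongs to the secondary, one-month visit. The null hypothesis is tested at week 4, where 10% is tolerated. This also stands, although the article does not say which visit's d will be used for planning.

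The illustrations are small beside sampling error. On the assumed SD and correlation, the SD of change is 2 × √(2 × 0.4) = 1.79 and the standard error of the difference is 1.79 × √(2/10) = 0.80. A bias of 0.30 is therefore under half a standard error. This limits the weight of the point but does not remove it: a confidence interval would show the sampling error, not the bias, and carried values would be counted as if observed.

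Four stronger readings are tempting and not supported:

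- *Early scores are frozen.* Someone who completes week 4 and does not return the postal form carries a week-4 score. Only early dropouts carry early scores.
- *The rule contradicts intention to treat.* Imputation is how the article keeps all randomised participants in the analysis, and the withdrawal text does not say that outcome collection stops.
- *Within-person correlations for planning are distorted.* The article plans Cohen's d and mentions no such use of correlations.
- *Bias is certain, or its direction known.* Neither follows without the course of pain and the pattern of loss by arm.

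**Conclusion.** The point holds in a limited form. The article fixes carrying forward as the sole method, so this is a stated choice and not detail left to another document. The choice can bias the planning effect size in either direction, but only if scores change after the carried visit and the trend or the loss differs by arm. A reader might take this to threaten the trial's main purpose or its primary endpoint to the extent of 40%. It does neither.

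The sizes in points, the SD and the correlation are assumptions, and the zero-bias cases also assume missingness unrelated to the scores. In the one-month relapse example the error would nearly halve a future trial, from 49 to 26 per arm. This is worth correcting because correction is cheap, and it is no reason to doubt the feasibility conclusions.

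**What to change.** 1. Base the effect estimate (difference, SD and Cohen's d, with a confidence interval) on observed scores, with n and missingness by arm and visit. Alternatively, use a simple likelihood-based repeated-measures model on all observed scores with baseline as a covariate. With 20 participants the first is proportionate, and the planned nonparametric tests can stay as a pilot of procedure on the observed data.
2. Keep last observation carried forward only as a sensitivity analysis.
3. Clarify that withdrawal in the section on withdrawals does not end outcome collection unless the participant withdraws consent. This concerns data collection only and leaves the clinical rule as it is.

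Neither estimate protects against loss that depends on unseen pain after the last form, so the missingness table matters.

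No new data are needed, since the weekly scores are already collected. The cost is a little more analysis work and wider intervals. For observed-only analysis with equal losses, the standard error grows by about √(10/9) = 1.05 at week 4 and √(10/6) = 1.29 at one month if the tolerated numbers are missing. That extra width reflects the data actually returned.
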